### Ethical Considerations

This study has been approved by the University of Hawaii Institutional Review Board (IRB; 2022-00909). We will only collect data from voluntary participants who sign an informed consent (parents) and assent (children) document during the intake session of the study. Participants whose videos will be shared for the 20 crowdsourcing tasks used to filter workers will be contacted by the study team to have a thorough discussion about the planned use of those videos. Workers who are qualified to rate the remaining videos for ≥1 question will be required to complete The Health Insurance Portability and Accountability Act training and The Collaborative Institutional Training Initiative training and will be required to encrypt their laptops using whole disk encryption. These workers will be added to the IRB protocol and will become official members of the study team after thorough training.

Although we will require participants to consent to sharing videos with crowd workers who have undergone thorough training, the clinical translation of this diagnostic system will require a more scalable approach that is sensitive to privacy concerns. We will experiment with privacy-preserving alterations to the curated videos to obfuscate identifiable information from the videos without degrading the feature-tagging performance of workers. Examples include pitch shifting the audio, which will allow workers to understand the content of the speech, and pixelating the video, which will obscure the participant’s background and face but would still allow workers to observe body movement patterns. We will measure the extent to which each privacy-preserving mechanism degrades the answers to each question.

We will deidentify the participant data and anonymize any personally identifiable information. All the data will be immediately uploaded to our secure and encrypted server on Amazon Web Services (AWS) [50], which is Health Insurance Portability and Accountability Act–compliant. A fully anonymized version of the data set will be released to researchers only after signing a data use agreement, which will be approved by the University of Hawai‘I Data Governance Office.

To ensure that the annotation task is manageable for crowd workers, each 15-minute video will be segmented into five 3-minute clips. During the profiling phase, crowd workers will be compensated US $0.50 per 3-minute video segment rated. Workers who are selected to continue rating videos in the primary portion of the study will be compensated US $0.05 per question answered per video segment, with the opportunity of a bonus of US $0.05 per question if the answer aligns with the clinician ratings for that question. These payment rates are consistent with practices in crowdsourcing research studies in the field of human-computer interaction, and our preliminary studies have shown that the retention rate for this level of compensation is >90% [10,42,49].

### Gamified Data Curation

#### Description

We will develop novel gamified social experiences to curate video data containing diagnostically rich information. Each of these games will impose the structure required to extract salient behavioral features that are comparable across peers. Each game will involve 2 participants interacting on the web application through both the game itself and socially through live video and audio. During gameplay, each participant’s camera and microphone will be turned on, and their video and audio will be displayed in a Zoom-style [51] feed to the other participant. The video and audio feeds will be recorded during each session, in addition to keyboard strokes and mouse movements.

Each game will correspond to a subset of targeted behaviors for data capture. The existing literature on “serious games” has documented the usefulness of certain games to capture behaviors related to psychiatric diagnostics, although these games are usually single player. An example is a Go/No-Go game, where the player presses the spacebar in response to a timed “go” prompt in the presence of auditory and visual distractions. This game has been shown to be a reliable estimate of attention, impulsivity, hyperactivity, and executive functioning when recording gaze behavior, response time, and correct reaction rate [52]. We will modify the game so that the “go” prompts are initiated by the social game partner rather than an automated computer, allowing for the capture of socially relevant features. The field of “serious games” for the assessment of psychiatric behaviors is vast, and therefore, we will base all games on previously published literature. However, many behavioral features that we will study will not be tied to a particular game but will rather be observable as a by-product of the social interactions between participants (eg, social anxiety).

One of 7 possible games will be administered each day. A complete list of games and the corresponding behaviors that each game is designed to measure is shown in Table 2.

**Table 2 table2:** List of previously validated data capture games that have successfully generated data relevant for distinguishing the targeted psychiatric conditions from neurotypical controls.

Game^a^	Targeted behaviors
Go/No-Go [52]	Concentration, impulsivity, hyperactivity, executive functioning, and reaction time
AULA Nesplora [52]	Process speed and motor activity
Plan-It Commander [52]	Planning and organization
Braingame Brian [52]	Working memory, cognition flexibility, and impulsivity
Charades [6]	Emotion evocation and recognition and restrictive and repetitive behaviors
Balloon Popping [53]	Visual motor coordination
Spot The Eyes and Face [53]	Eye contact and face gaze
Free-form conversation^b^	Social anxiety, difficulty with social skills, speech delays, and language narrative

^a^As the games themselves are not central to the innovation of this proposal, details of the gameplay can be found in corresponding references [6,52,53].

^b^Free-form conversation will naturally occur across all games.

The design of the games will be conducted in consultation with a team of practicing clinical psychiatrists at the University of Hawai‘i School of Medicine, including [name], who is the chair of the Department of Psychiatry and who specializes in digital technologies for pediatric and adolescent psychiatry, as well as [name], who is an assistant professor in the Department of Psychiatry and who has experience with digital health solutions for psychiatry.

A minimum of 15 minutes of gameplay will be required each day, although participants may elect to participate for longer. To facilitate consistent data capture across possible computer, microphone, and camera configurations, a pertinent step for enabling comparisons across participants, a calibration program will be developed that will require each participant to align the camera’s zoom and their body position before each session. We will extensively test the calibration procedure before the study.

#### Participant Recruitment and Management

We plan to recruit a total of 400 study participants, comprising 100 individuals formally diagnosed with ADHD, another 100 diagnosed with ASD, a further 100 diagnosed with both ASD and ADHD, and 100 individuals evaluated and confirmed to not have any socially related psychiatric conditions. Our inclusion criteria are as follows: (1) adolescents aged between 14 and 18 (inclusive) years and (2) formally evaluated for ADHD and ASD by a licensed clinician with available documentation. The selection of the final 400 participants that comprise our core data set will be based on the personal information that participants are asked to disclose. Such metadata will be used to ensure a data set that is balanced with respect to race, ethnicity, and gender. The number of participants is based on testing the ability of our system to discriminate between groups of participants. As these groups are balanced, we set the prevalence for binary classification between each condition to 50%. Following a CI of 95%, an estimated theta of 95% [42,48,49], and a width of 15%, the sample size to compute the area under the receiver operating characteristic curve (AUROC) should be 37 [54]. Considering that we have 400 participants, with 100 participants per group, this enables us to follow a common 60:20:20 (train, validation and test ratio respectively) randomized split on the data. That is, we have a sample size (test set) of 40 participants to verify the system’s ability to discriminate between the neurotypical participants and the participants who were diagnosed with either ASD, ADHD, or comorbid ASD and ADHD.

Although formal and well-established methods to perform power calculations for ML analyses have yet to be established, most digital diagnostics studies for conditions such as ASD include <100 participants per class in binary classification [47]. We aim to maintain a similar sample size per diagnostic category. The digital social experiences will be delivered to study participants for 15 minutes each day for a 3-week duration, with a single game out of the 7 possible delivered each day. At least 3 distinct 15-minute sessions will be collected per game for each participant, allowing for comparisons across days for analysis of within-peer consistency.

Given the remote delivery of the data collection, a critical challenge will be to ensure that all participants will have a social partner when logging into the study system. The participants will be asked to log in at a particular time each day to be scheduled in advance of the first day of the study. We will host 10 separate time slots and 3 makeup time slots every day of the study, and participants will be automatically matched with a partner during log-in.

#### Evaluation

We will evaluate the data curation system for (1) compliance of participants with respect to the study procedures during each session and (2) global participation rates. To measure compliance, we will run computer vision face detection algorithms in conjunction with skeletal pose estimation using MediaPipe [55] Python library to ensure that each participant’s face, upper torso, and shoulders are fully visible and will calculate the percentage of valid frames across sessions per participant. To measure participation across sessions, we will record the total number of sessions with both participants and the mean session time. In addition to these quantitative analyses, we will run qualitative pilot user studies to understand participants’ experiences about the data collection game process, including questions about the entertainment value provided by the games, the usability of the participant matching and scheduling system, and open-ended feedback.

### Novel Crowd-Powered and Traditional ML-Based Feature Extraction

#### Description

We will create 2 pipelines for converting raw video and audio data into interpretable feature vectors that quantify social behavior relevant to ADHD and ASD diagnostics. For behaviors that can be feasibly quantified using computational methods, we will use existing toolkits. For highly complex and nuanced social behaviors that are beyond the scope of current ML tools but that are highly relevant to psychiatric classification, we will use a novel crowdsourcing pipeline to match crowd workers to labeling tasks.

We will perform automatic feature extraction for behaviors potentially related to diagnoses such as the percentage of total conversation time contributed by the participant, eye gaze patterns during the gameplay including the proportion of gaze directed toward the game versus the live video feed of the other participant, vocal prosody and intonation during conversation, natural language processing analysis of the content of the conversation after converting raw audio to text using speech-to-text programs, and breaks in task flow as measured by pauses in game-related keystrokes and mouse movements. The extracted information will be stored for each frame at a sampling rate of 5 frames per second. As depicted in Figure 2, each of these features will be concatenated into a temporal feature vector and used to train a time series DL model such as a long short-term memory recurrent neural network or an attention-based model (eg, transformers). There are existing Python libraries that enable the proposed automatic behavioral feature extraction such as OpenFace [56] and MediaPipe for eye gazing. For facial emotion recognition, we will use Amazon Rekognition [57], an AWS service that provides recognition of disgust, happiness, surprise, anger, confusion, calmness, and sadness in addition to other relevant facial features such as whether the eyes and mouth are open. In the audio domain, pitch will be extracted using the Convolutional Representation for Pitch Estimation library [58], and waveforms will be processed using the librosa library [59].

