### Multicondition Diagnostics With Adaptive Input Querying

#### Description

We will develop DL models for the multilabel classification of ADHD and ASD, which can emit four possible outcomes: (1) ADHD, (2) ASD, (3) ADHD and ASD, and (4) neither condition. The models will also output the behavioral characteristics that led to the final classification decision by producing the 95% CI of each behavior as derived from both crowd workers and automated computational models. This will involve synthesizing multiple sources of inputs and communicating the result to the end user in a manner that is understandable to the patient or the caregiver. The confidence scores will enable the model to adaptively request more data from the patient and to be specific about which types of data are needed.

To derive an interpretable quantification of each behavioral feature, we will collect clinical categorical ratings of each behavior by licensed psychiatrists at the University of Hawai‘i at Mānoa. We will compensate the psychiatrists for their service and will use the mean of the crowd worker responses as a baseline method for deriving the interpretable quantification of each behavior. Although this method could be sufficient, it is possible that crowd workers have varying levels of rating abilities depending on the qualities of the video and the qualities of the crowd workers themselves. Therefore, we will explore the use of the crowdsourced ratings themselves combined with crowdsourcing metrics derived from worker performance and the computationally generated behavioral features as collective inputs into an ML model for each behavior. Such metrics will include the time spent by each worker providing the annotations for the video, worker rating history for each question, and variability in the worker’s answers across videos and within a particular video. It has been previously shown that these crowdsourcing metrics and similar metrics have predictive power in a crowd worker’s annotation quality [11]. We will test whether the ML model is a better predictor than the crowdsourced ratings alone. The loss function for the ML model for individual behaviors will optimize with respect to the mean clinician rating per behavior.

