### Limitations

Although our initial findings are optimistic, there are some limitations to the study. The primary challenge will be the recruitment and retention of 400 study participants, including the formal clinical validation of the diagnosis for each participant. Although this study can be successfully completed with fewer participants, smaller data sets can affect the model’s learning capability, leading to overfitting, noisy outliers, or sample bias. To help manage this recruitment effort, we will hire a full-time clinical research coordinator to recruit and manage the participants. We will work with the clinical collaborators in the Department of Psychiatry to recruit in Hawaiʻi’s psychiatric clinics, where our collaborators and their colleagues practice. This will be supplemented with web-based recruitment using targeted advertisements on social media. We have discussed this recruitment plan and desired study size with our collaborators in the Department of Psychiatry, and we hold recurring monthly meetings to strategize about participant recruitment using both our existing access to several clinics in Hawaiʻi and web-based targeted recruitment. In addition, our former mentor and collaborator, [name] at Stanford University, has access to hundreds of families with adolescent children diagnosed with ASD as well as comorbid ADHD. He is the founder of Cognoa [53,64-69], an artificial intelligence–based digital diagnostic tool for studying early childhood development and pediatric behavior.

There might be technical challenges associated with web applications or user interfaces, which may occur at later stages of the study. The proposed data curation game platform may lack qualities that would garner repeated participant engagement over a 3-week period, such as poor user interface design, poor design of the automated notification system, or poor entertainment quality of the individual games. To mitigate this risk, we will run several iterative design sessions regarding proper implementation of the design process to maximize both user engagement and high-fidelity data collection. We will run several pilot studies to obtain both qualitative and quantitative measures of engagement before running the primary data collection study.

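### Conversation content is a classifier input and stays intelligible to raters, with no stated safeguard against spoken mention of a diagnosis made before enrolment, so label leakage cannot be excluded

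*Protocol article*

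**What the plan says.** All references are to the protocol article.

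- **Label.** Under Participant Recruitment and Management, every participant must be aged 14 to 18 and "formally evaluated for ADHD and ASD by a licensed clinician with available documentation". The diagnostic group is fixed before any recording.
- **Speech.** Under Gamified Data Curation, two participants interact live in each game. "The video and audio feeds will be recorded during each session, in addition to keyboard strokes and mouse movements". A footnote to Table 2 adds: "Free-form conversation will naturally occur across all games". No limit on topics is stated.
- **Automatic features.** Under Novel Crowd-Powered and Traditional ML-Based Feature Extraction (Description), the list includes "natural language processing analysis of the content of the conversation after converting raw audio to text using speech-to-text programs". Then "each of these features will be concatenated into a temporal feature vector and used to train a time series DL model". Prosody and share of talking time are listed separately, so what is said is a predictor in its own right.
- **Human ratings.** Under Ethical Considerations, one privacy alteration is "pitch shifting the audio, which will allow workers to understand the content of the speech". The Evaluation paragraph of the feature-extraction section has workers rate the unaltered video as well, after the altered one.
- **Psychiatrists.** Under Multicondition Diagnostics With Adaptive Input Querying (Description), the team will "collect clinical categorical ratings of each behavior by licensed psychiatrists"; these ratings are the target of the behavior models. Limitations says that recruitment takes place in clinics "where our collaborators and their colleagues practice".
- **Stated protection.** Ethical Considerations provides for removal of personal identifiers. It does not mention spoken references to a diagnosis.

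**The concern.** An accuracy study needs an index test that does not contain the reference standard. Here the label exists before the recording, the participant probably knows it, and the words spoken are both a model input and audible to the human raters. Removing names and faces does not remove a sentence in which someone says they have ADHD.

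Two results are exposed. The first is the headline accuracy. Leaked labels raise it, and resampling participants does not help because the same kind of cue occurs in training and test sets. The second is the central hypothesis that combined features beat automated-only or human-only features. Disclosure can enter both feature types, so the comparison may be distorted in a direction that cannot be predicted.

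The tool is meant to shorten the time to diagnosis. Its intended user has no diagnosis to mention, so performance gained through disclosure would disappear in use.

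**Working it through.** **The plan's own figure.** Participant Recruitment and Management gives 37 participants for an AUROC of 0.95, a 95% CI of width 0.15 and 50% prevalence. The condition is 2 × 1.96 × SE ≤ 0.15. The Hanley-McNeil and the Newcombe standard errors both give width 0.1508 at n = 36 and 0.1486 at n = 37, so 37 is reproduced. At the 40 participants of the test set the width is 0.143. This calculation covers sampling error only. Leakage is a bias, and it leaves n = 37 unchanged.

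**Path from label to prediction.**
1. The label precedes recording (inclusion criteria).
2. Participants probably know it. This is inferred from the prior formal evaluation, the age range and the assent procedure; the article does not state it.
3. Unscripted talk is recorded in each session (Gamified Data Curation; Table 2 footnote).
4. Its content enters the feature vector (feature-extraction Description).
5. Raters can understand it (Ethical Considerations; feature-extraction Evaluation).
6. No stated step removes mentions of a diagnosis.

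**Exposure.** 3 weeks × 7 days = 21 sessions; 21 × 15 min = 315 min = 5.25 h. This is game time, and the amount of free talk within it is not given. If the chance of disclosure per session is r and sessions are independent (both assumed), the share disclosing at least once is 1 − (1 − r)^21:

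| r (assumed) | share over 21 sessions |
|---|---|
| 1% | 19% |
| 2% | 35% |
| 5% | 66% |

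**Size.** Let A be the AUROC without leakage and q the fraction of cases revealed. Suppose each revealed case ranks above every control and no control is revealed. A random case-control pair is then ordered correctly with probability 1 when the case is revealed, and with probability A otherwise:

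observed AUROC = q + (1 − q) × A

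| q (assumed) | A = 0.80 | A = 0.85 |
|---|---|---|
| 0 | 0.80 | 0.85 |
| 10% | 0.10 + 0.90 × 0.80 = 0.82 | 0.865 |
| 20% | 0.20 + 0.80 × 0.80 = 0.84 | 0.88 |
| 30% | 0.30 + 0.70 × 0.80 = 0.86 | 0.895 |

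The values of A are illustrative. The result is an upper bound for disclosure by cases, because it assumes that every disclosure is fully exploited and that the cue never points to a control.

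**The case against.** The article nowhere says that participants disclose a diagnosis or that raters are given one. A condensed article may leave masking and session instructions to the full protocol. **This stands in part.** A reader might infer that neither raters nor model are blind to the label, or that treatments are being discussed. The text supports neither. What remains does not rest on silence: the article chooses spoken content as a predictor and intelligible speech for raters, and it pairs these with a label that participants probably know.

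A reader might also take the 5.25 hours as free conversation. It is structured play in which conversation also occurs.

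The AUROC formula is generous. Controls must also have been formally evaluated for both conditions and may mention assessments, and the partner's voice is in every session, so a diagnostic term does not mark cases only. The formula is binary, whereas the target has four classes, and a vague remark about care would not separate ASD from ADHD. **This stands**, and the figures must not be read as an expected effect.

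The rater route is diluted. Sessions are cut into five 3-minute clips, which makes 21 × 5 = 105 per participant if all are used, so a single remark reaches one clip. Workers also tag behaviors and are not asked for diagnoses. **This stands**: the effect through ratings may well be smaller than through the language features.

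Finally, a reader might infer that psychiatrists will rate their own patients and that this corrupts the selection of workers. The overlap is only possible. Recruitment also runs through web advertising and a collaborator at another university, and the label needs a licensed clinician, who need not be one of the raters. The worker filter uses pilot-test videos, so the inference from recruitment of the 400 participants does not reach it.

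**Conclusion.** The concern holds as a risk that the plan leaves open. Followed as written, any spoken mention of a diagnosis enters the language features and can enter the human ratings, and the planned Monte Carlo cross-validation would not detect it. Leakage therefore cannot be excluded, and the part of performance that it produced would not transfer to undiagnosed users.

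The size is unknown because the disclosure rate is not in the document. For a true AUROC of 0.80 the upper bound is +0.02 at q = 10% and +0.04 at q = 20%, and there is no bias at q = 0. The conclusion rests on one inference, that most diagnosed participants know their diagnosis, and on the absence of any stated safeguard beyond removal of identifiers. It does not show that disclosure will occur or that raters are unblinded. The change should be made before data collection, because ratings given after hearing a disclosure can be repaired only by re-rating.

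**What to change.** 1. **Instruction.** Before sessions, ask participants not to mention diagnoses or related care.
2. **Screening.** Search the transcripts, which are produced anyway, for a fixed list of terms. Drop flagged segments from the language analysis and from the rated clips. Do this so that no mask token, silent gap or count of removals remains as a feature. Masking or muting alone can leave a marker that itself reveals the label.
3. **Sensitivity analysis.** Report diagnostic performance without content-based language features and without flagged sessions. Include the comparison of combined, automated-only and human-only models. Also report how often flags occurred in each diagnostic group, which supplies the missing disclosure rate.
4. **Psychiatrist ratings.** Provide coded clips without the diagnosis. Where raters and recruiting clinics overlap, do not assign a rater any participant known to them.

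The cost is a sentence in the session instructions, a term filter on existing transcripts, an assignment rule and one additional analysis. The downside is a little lost data and possibly a lower reported AUROC. The Results section says that the recording features are still being finalized, so the change can still be built in.
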